## Methods

### Study design

Managing Diabetes is a ‘Flash’ is a two phase study programme consisting of a multi-centre randomised, parallel-group study consisting of a 6-month comparison between SMBG and FGM, including a 6-month continuation phase (see Fig. 1). Once enrolled, the total study period is 12 months for each participant (12 months of FGM for the intervention group will enable an investigation of sustained FGM outcomes). During the continuation phase, the FGM group will continue the intervention for a further 6 months and the control group will cross over and receive a 6-month FGM intervention. The primary purpose of offering FGM to the control group at 6 months is to encourage retention and engagement.

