### Sample size

Based on our data from an earlier study in this population, the standard deviation of HbA1c amongst those with values 75 mmol/mol (≥9%) or greater (and irrespective of self-monitoring blood glucose frequency) was 18.6 mmol/mol [38, 39]. Assuming a correlation between repeated measures of 0.7, a sample size of 58 (29 per group) would provide 80% power to detect a difference in mean changes for HbA1c of 1% (10.93 mmol/mol) using a two-sided test at the 0.05 level. This would be considered a clinically important difference, of a similar magnitude to other proven technologies such as insulin pumps or CGM [40]. To account for a small amount of missing data and loss to follow-up (anticipated to be < 10%), we will recruit a sample size of 64 (32 participants per group) at baseline. Reasons for non-retention of participants (i.e., consent withdrawn, moving outside of the study DHBs, or lost to follow-up) will be recorded and shown in a CONSORT flow diagram (Fig. 1).

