### Outcome measures

The primary outcome measure is the difference in change in HbA1c between groups at 6-months.

All other measures are for secondary and tertiary (exploratory) outcomes. The timing of all assessments is presented in Table 2.

**Table 2 Tab2:** Managing Diabetes in a ‘Flash’ schedule of assessments

	Time point				
Outcome	Baseline	3 m	6 m	9 m^a^	12 m^a^
Adverse events					
Cutaneous, diabetic ketoacidosis, severe hypoglycaemia	Every 2 weeks from baseline				
Device performance					
FGM/SMBG device malfunctions, FGM sensor failures	Every 2 weeks from baseline				
Clinical					
Glycaemic control	X	X	X	X	X
Height	X	X	X	X	X
Weight	X	X	X	X	X
Glucose monitoring behaviour					
Blood glucose monitoring	X	X	X	X	X
Interstitial glucose monitoring		X	X	X	X
Habitual sleep and physical activity					
Sleep	X	X	X		
Physical activity	X	X	X		
Participant reported					
Diabetes treatment satisfaction	X	X	X		X
Fear of hypoglycaemia	X	X	X		X
Flash glucose monitoring acceptability		X	X		X
Health-related quality of life (generic)	X	X	X		X
Health-related quality of life (diabetes-specific)	X	X	X		X
Sleep quality and quantity	X	X	X		X

^a^ Denotes continuation phase of study

Abbreviations: *FGM* Flash glucose monitoring, *SMBG* self-monitoring blood glucose

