### Statistical analysis

Means and standard deviations (SDs) will be reported for continuous variables (i.e., age, diabetes duration, HbA1c, glucose monitoring behaviour, questionnaire scores) that are approximately normally distributed, geometric means and SDs for those that are approximately log-normally distributed, and medians and IQRs otherwise. Categorical variables will be described as the number and percent of participants in each category (i.e., gender, ethnic group, insulin regimen). Adverse events will be categorised by the type of event (e.g., severe hypoglycaemia, DKA, sensor insertion issues, sensor wear issues). The frequency of events will be reported by event category.

A mixed linear model will be used to test the difference in HbA1c, with the primary outcome being at 6-months, between the intervention and control groups, using data from all time points with a random participant effect used to accommodate the repeated measures and a group-time interaction to model differences in longitudinal changes. Changes in number of glucose measurements performed and patient-reported outcome measures (i.e., PedsQL generic core scale, PedsQL diabetes module, HFS, and DTSQs scores) from baseline through to 6 months will be calculated by comparing scores from control and intervention group participants using Poisson (or negative binomial regression if there is evidence of over-dispersion) for count outcomes and linear mixed models for continuous outcomes with all collected data included. Model residuals will be examined along with the distribution of random effects. If residuals are positively skewed, natural logarithmic transformations will be investigated and retained if these improve the satisfaction of model assumptions. Mixed quantile regression will be investigated for continuous outcomes if issues with model residuals remain following such transformations. If HbA1c values of 130 are observed, mixed Tobit models with right censoring at 130 will be used for this outcome instead. All mixed models will use restricted maximum likelihood (REML) estimation for the variance components.

Some secondary analyses, such as those involving the wait-list control after they cross over, will only include participants from one group and so group (and group-time interaction) terms will not be included in these models.

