The main analyses will follow a modified intention- to-treat principle with all participants analysed in the group to which they were randomised, regardless of actual sensor wear. Per protocol analyses will be also be investigated by including only those from the FGM group who scanned at least 12 out of 14 days in the two weeks prior to the 6-month study visit and excluding any participants from the SMBG group who used FGM at any time during the study. All models will include variables used in minimization [59].

Any missing HbA1c values will be imputed using multiple imputation with chained eqs. (100 imputations after at least 100 burn-ins) and with the imputation model including: gender, HbA1c status at baseline as well as values of that variable from other time points, insulin regimen, frequency of self-monitored glucose (capillary or interstitial) and socioeconomic status. If missing data exceeds 10%, plausible scenarios involving informative missing data will be investigated to explore the robustness of findings.

Statistical analyses will be performed using R 3.5.2 or Stata 15.1 software (or later versions) with two-sided *p* < 0.05 considered significant. To maintain the integrity of the study, statistical analyses will be performed by the biostatistician blinded to group allocation.

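### The listed imputation model for missing HbA1c omits randomised group, which under missing at random pulls the primary 6-month difference modestly towards zero

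*Protocol article*

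**What the plan says.** All places are in the protocol article.

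- **Outcome measures:** "The primary outcome measure is the difference in change in HbA1c between groups at 6-months".
- **Statistical analysis, primary model:** a linear mixed model with a random participant effect and "a group-time interaction to model differences in longitudinal changes".
- **Statistical analysis, missing data:** "Any missing HbA1c values will be imputed using multiple imputation with chained eqs", with 100 imputations. The "imputation model including: gender, HbA1c status at baseline as well as values of that variable from other time points, insulin regimen" continues with "frequency of self-monitored glucose (capillary or interstitial) and socioeconomic status". Neither randomised group nor imputation by arm is mentioned. Scenarios with informative missingness are added only if more than 10% is missing.
- **Statistical analysis, covariates:** all models are to contain the minimisation variables. According to Randomisation these are gender and HbA1c band, not arm.
- **Randomisation:** the statistician works with uninformative group codes until the planned analyses are done.
- **Study design:** from month 6, "the control group will cross over and receive a 6-month FGM intervention".

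**The concern.** An imputation model should contain every term whose effect the analysis model estimates. Here the analysis estimates an arm difference, and the listed imputation model has no arm term. Missing 6-month values in both arms then come from one shared equation. That equation carries the arm difference only as far as the listed predictors happen to carry it.

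Two listed predictors can act as partial stand-ins for arm, but neither is dependable.

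- **Monitoring frequency** should differ by arm if FGM works as hypothesised. It is downloaded at study visits for the preceding two weeks, so it is likely to be missing when the visit is missed.
- **HbA1c at other visits** helps if month 3 is observed. Read literally, it also takes in months 9 and 12, when both arms use FGM and the values no longer separate the arms as they stood at month 6.

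At stake are some attenuation of the primary estimate and some loss of power, in a design that has about 80% power and little to spare. Under missing at random, the mixed model fitted to the available data would not have this bias, so the imputation step would introduce it.

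**Working it through.** **1. Inputs (Sample size section).** The SD of HbA1c "was 18.6 mmol/mol". "Assuming a correlation between repeated measures of 0.7, a sample size of 58 (29 per group) would provide 80% power" for a difference of 10.93 mmol/mol, two-sided 0.05. Missing data and loss to follow-up are anticipated below 10%, and 64 are recruited.

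**2. The plan's own figure reproduces.** SD of change = 18.6 × √(2 × (1 − 0.7)) = 14.41. With 29 per group the standard error is 14.41 × √(2/29) = 3.78 and the noncentrality is 10.93/3.78 = 2.89. The t-test power is 0.810, against 0.796 with 28 per group. So 29 per group is right.

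**3. Attenuation formula.** Let m be the share missing at month 6, equal in both arms and missing completely at random. Let k be the arm difference that the imputed values carry. The expected estimate is

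(1 − m) × 10.93 + m × k.

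With group in the imputation model, k = 10.93 and nothing is lost.

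**4. Only baseline HbA1c informs the imputation** (month 3 and frequency also missing). Baseline is balanced by randomisation, so k = 0.
- m = 0.10: 0.9 × 10.93 = 9.84, a loss of 1.09 (10%).
- m = 0.20: 0.8 × 10.93 = 8.74, a loss of 2.19 (20%).

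**5. Month 3 observed, all pairwise correlations 0.7.** Given baseline, the within-arm variance of month 3 is 18.6² × (1 − 0.49) = 176.44. Its covariance with month 6 is 18.6² × (0.7 − 0.49) = 72.65. Leaving group out adds the between-arm parts to both.
- Full effect already present at month 3: slope = (72.65 + 10.93²/4)/(176.44 + 10.93²/4) = 102.52/206.31 = 0.497, so k = 0.497 × 10.93 = 5.43. The estimate at m = 0.10 is 9.84 + 0.54 = 10.38 (5% loss).
- Half the effect at month 3 (5.465): slope = (72.65 + 14.93)/(176.44 + 7.47) = 0.476, so k = 2.60. The estimate is 10.10 (about 7.5% loss).
- Full effect at month 3, with an assumed month-3 to month-6 correlation of 0.85: covariance = 18.6² × 0.36 = 124.55, slope = 154.42/206.31 = 0.748, k = 8.18. The estimate is 10.66 (2.5% loss).

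**6. Large-sample simulation** (1,000,000 records, missing completely at random, stochastic regression imputation, ANCOVA on the completed data). The separation of monitoring frequency between arms is an assumption, shown as a range.

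| Information used, no group | 10% missing | 20% missing |
|---|---|---|
| Baseline only | 9.82 | 8.78 |
| Baseline + month 3, half effect | 10.11 | 9.28 |
| Baseline + month 3, full effect | 10.38 | 9.81 |
| As above + frequency, arms 1 SD apart | 10.47 | 10.00 |
| As above + frequency, arms 2 SD apart | 10.67 | 10.32 |
| **Group included** | **10.88** | **10.95** |

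The first three rows agree with the formula within simulation error. A separate large-sample run gave 9.85 (baseline only), 10.41 (month 3 observed) and 10.26 (months 3, 9 and 12 observed) at 10% missing, against about 10.96 with group.

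**7. Small-sample check** (32 per arm, chained equations). Attenuation was 1.05 when 10% missed both months 3 and 6, and about 2.1 when 20% did. When only month 6 was missing and visits up to month 6 were used, it was just 0.1 to 0.2. Adding group left −0.06 to 0.04.

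**8. Power at the attenuated effect, 29 per group.** It is 0.72 (at 9.82) to 0.79 (at 10.67) at 10% missing, and 0.63 (at 8.78) to 0.76 (at 10.32) at 20% missing, against 0.81. The standard error is held at its planned value throughout.

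**The case against.** **The list may not be complete.** It is introduced as what the model includes, not as all that it contains, and a journal article condenses the full protocol. A reader might infer that the plan excludes group, and it does not say so. But the article fixes the method, the number of imputations and a named predictor list down to socioeconomic status. An analyst who follows it would leave group out, and nothing elsewhere puts it back.

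**The primary analysis may be the mixed model on available data.** The objectives section speaks of using all available data, and that model is free of this bias under missing at random. However, the missing-data paragraph applies imputation to any missing HbA1c without calling it a sensitivity analysis, so the text does not keep imputed values out of the primary result.

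**Direction depends on who is missing.** A reader might infer that every imputed value pulls the estimate towards zero. The documents do not support that. Participants who withdraw return to usual care. If 10% in each arm drop out and the FGM dropouts lose the effect entirely (an assumption), the true effect by randomised group is 0.9 × 10.93 = 9.84. Imputing without group from baseline alone gives about 9.84, while imputing with group gives about 10.93, which is 11% too high. This stands as a limit on the claim. It is not an argument for leaving group out: the agreement is accidental, and the available-data mixed model makes the same missing-at-random assumption. Such departures belong in an explicit sensitivity analysis.

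**The size is modest.** With 32 per arm the standard error is 14.41 × √(2/32) = 3.60, so the largest loss at 10% missing is about 0.3 standard errors. The error is also conservative: it does not create a false claim of benefit. Both points stand.

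**Conclusion.** The point holds as a moderate one. The imputation model as listed is not compatible with the primary analysis model, because it omits the variable whose effect is being estimated. Under missing at random, with the protocol's SD, correlation and effect, the 6-month difference is attenuated by about 2% to 10% at 10% missing and by up to about 20% at 20% missing. Where in the range it falls depends on whether month-3 HbA1c and monitoring frequency are observed for those who miss month 6. The documents give no missing share by visit, so this remains an assumption.

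Two stronger readings are not supported. It cannot be said that the primary result will be seriously biased: the anticipated missingness is below 10%, and the worst case needs month 3 to be missing as well. Nor do months 9 and 12 have to be dropped as predictors. They are poor substitutes for arm after the crossover, but once group is in the model that restriction is optional.

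**What to change.** State in the imputation paragraph that the coded randomised group is in the imputation model for HbA1c at every visit, or that imputation is done separately within each arm. In a wide-format chained-equation model, a group term in each visit's equation lets the arm difference vary by visit, which matches the group-by-time term in the analysis. The uninformative group codes are enough, so blinding is unaffected. Restricting the HbA1c predictors to visits up to month 6 may be added but is not required.

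The cost is one line of text before analysis, with no extra data, visits or participants.

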#### Post-trial care

Should this study provide evidence of the effectiveness of FGM, it will be ideal to provide ongoing funded access to FreeStyle Libre sensors to study participants and other young people with T1D (FGM is currently not publically funded within New Zealand). In preparation for this study, discussions have begun with PHARMAC (the New Zealand government agency that decides which medical devices to publicly fund in New Zealand) on publically-funded access to FGM.

## Discussion

Adolescence is a challenging time for diabetes management and adherence. Flash glucose monitoring technology may assist adolescents with self-monitoring glucose levels and inform treatment decisions that result in improved glycaemic control. *Managing Diabetes in a ‘Flash’* is a 12-month study that will combine a 6-month RCT, immediately followed by a 6-month observational continuation study. There are several strengths of the study, including: 1) being funded and conducted independent of the FreeStyle Libre manufacturer; 2) the RCT design, which is the gold standard for evaluating the effectiveness of interventions such as FGM; 3) the 6 month duration of the RCT and observational studies allowing for insight into effects following an initial “novel” period, 4) the waitlist control group who will access the intervention at 6-months, which may maximise study retention; 5) no additional diabetes support to the intervention group beyond providing the FGM system; and 6) the real-life context which will help gauge the effectiveness of FGM among adolescents with suboptimal glycaemic control. The observational phase enables the longest evaluation of FGM in this patient population to date, enabling research of whether or not outcomes at 6 months appear to be sustained at 12 months despite the lack of a control group for this comparison. Overall, the study outcomes are wide in scope and will provide a broad evaluation of the application of FGM among young people with T1D that provide valuable evidence to inform shared decision making between the patient, their family/families, the clinical team, and healthcare funders.

## Abbreviations

BMI: Body mass index
DHB: District health board
DKA: Diabetic ketoacidosis
DTSQc: Diabetes Treatment Satisfaction Questionnaire-status version
DTSQs: Diabetes Treatment Satisfaction Questionnaire-change version
FGM: Flash glucose monitoring
HbA1c: Glycated haemoglobin
HFSC: Hypoglycaemia Fear Survey for Children
HFS-II: Hypoglycaemia Fear Survey-II
IQR: Interquartile range
MVPA: Moderate-vigorous physical activity
PedsQL: Paediatric Quality of Life Inventory
PSQI: Pittsburgh Sleep Quality Index
REDCap: Research electronic data capture
REML: Restricted Maximum Likelihood (also Residual Maximum Likelihood)
SD: Standard deviation
SMBG: Self-monitoring blood glucose
T1D: Type 1 diabetes
